## Research goals

The first goal of this randomized controlled trial is to compare the efficacy of two online training programs promoting recovery from work. We hypothesize that participants in the two experimental conditions (CBT-based and mindfulness-based training) will experience lower levels of work-related PT (primary outcome) after the intervention. No prediction can be made from previous literature as to which of the two interventions would be more effective. Therefore, we assume that the two experimental conditions will not differ with regard to their effectiveness in reducing the primary outcome.

The second goal of the present study is to explore the mechanisms related to recovery from work and its improvement on a daily level. Hence, using the data from the experience sampling phases of the study, we will investigate within- and between-day variables and processes that may account for the overall effect of the intervention—and, in addition, may further qualify the expected effect.

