### Participants and recruitment

The study will be conducted with employed volunteers recruited through newspapers, flyers, and social media. To estimate the power to detect an assumed meta-analytical pre-post effect of *d* = 0.36 [42], if such an effect exists in the population, we ran a Monte Carlo simulation. Our analyses for the primary outcome involve a Latent Change Model (see below for more details). The simulations showed that for a two-tailed test with 90% power and a priori alpha level of 5%, we would need *N* = 136 participants in each experimental group to be able to detect a pre-post difference of approximately *d* = 0.35 (in our case represented by the intercept of the latent change factor) if it exists in the population.

In addition, for the analyses of the dynamic associations with the measurement bursts, previous studies have shown that the power to detect a relatively small standardized indirect effect of 0.1 was = 0.81 for ICC ≥ 0.10 with *J* ≥ 100 clusters with a within-cluster sample size of *n *_*j*_ = 20 [56]. Because our research questions refer in part to the upper levels of the hierarchical data, we will need a sample size that will allow us to estimate unbiased parameters for the mediation models at the person-level of analysis as well. Li and Beretvas [57] showed that a multilevel SEM required at least 80 clusters to circumvent convergence issues.

Considering all the analyses' requirements and assuming a drop-out rate of up to 20% after Phase 3 and up to an additional 20% after Phase 4, we aim to recruit 600 participants (i.e., 480 in Phase 4 and 384 in Phase 5). The analyses will be conducted using all available data (either with Full Information Maximum Likelihood or Bayesian estimation). To be eligible for this study, participants must (1) be 18 years or older, (2) be working regular working hours (no shift work) at least part-time, (3) not be in psychotherapeutic or psychiatric treatment, and (4) be smartphone users with mobile internet access. In addition, participants must be able to read and write in German.

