### Data analyses

Our research goals refer to different levels of the data. Besides evaluations of the interventions’ efficacy, one part of our research involves hypotheses on the within-day level. By contrast, others focus on the same processes between days and several weeks. We will address the complexity of our data by applying various statistical approaches.

To evaluate changes across time in primary and secondary outcomes, we will use the pretest, posttest, and follow-up measures. These measures represent indicators of latent variables estimated separately in the two experimental groups and the two waitlist control groups combined. Using the latent variables (latent states), we will set up Multigroup Latent Change Models (with baseline-change and neighbor-change variants). Latent Change Scores from (a) pretest to posttest and from pretest to follow-up (baseline-change) and (b) from pretest to posttest and from posttest to follow-up (neighbor-change) will provide information about the effect sizes from pre to post and on the maintenance of the effects from posttest to follow-up [86]. To estimate the models, we will use the Bayes estimator as implemented in Mplus [87]. We will determine the convergence diagnostic [88], evaluate potential convergence issues by doubling the number of iterations, and visually inspect histograms for all parameters and the trace plots for the Markov chains. For the difference between the pre-post change scores in both experimental groups, we will set up an informative prior with a normal distribution, a mean of zero, and a small variance, that is, *N*(0, 0.010). This prior corresponds to the assumption that the change scores in the two groups should be equal, implying similar efficacy between the two interventions. A small variance around the mean of the prior will reflect our confidence that the difference between the change scores will be minimal but will allow for small differences [89]. This distribution implies that 95% of the standardized differences in the means ranges from -0.2 and 0.2. Accordingly, the efficacy of the two interventions will be considered equal if the standardized difference in the latent change scores based on the posterior distribution lies within a range of -0.2 and 0.2.

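### The range that decides equality of the two programs is the 95% range of the prior placed on their difference, so the rule is met before any data

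*Protocol article*

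**What the plan says.** All of the following is in the Protocol article.

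- **Prior (Data analyses).** For the difference in pre-post change between the two experimental groups, the analysts will use "an informative prior with a normal distribution, a mean of zero, and a small variance, that is, *N*(0, 0.010" (the second figure being the variance).
- **Rationale (Data analyses).** "This prior corresponds to the assumption that the change scores in the two groups should be equal, implying similar efficacy between the two interventions".
- **Width (Data analyses).** "This distribution implies that 95% of the standardized differences in the means ranges from -0.2 and 0.2".
- **Decision rule (Data analyses).** It follows directly from the stated width: "the efficacy of the two interventions will be considered equal if the standardized difference in the latent change scores based on the posterior distribution" falls in the same range. The closing words are "based on the posterior distribution lies within a range of -0.2 and 0.2". The rule names neither a point estimate nor an interval, and no other reason for 0.2 is given.
- **Background to the hypothesis (Research goals).** Comparing the two programs is the first goal. "No prediction can be made from previous literature as to which of the two interventions would be more effective", and from this the article moves to assuming no difference.
- **Sample (Participants and recruitment).** "we aim to recruit 600 participants (i.e., 480 in Phase 4 and 384 in Phase 5", with two thirds of participants allocated to the two experimental arms.

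**The concern.** An equality rule should be hard to satisfy unless the data show that the difference is small. Here the margin is the prior's own 95% range, and the decision is read from a posterior that contains that prior. If the trial collected nothing, the posterior would equal the prior and the rule would be met, whether read as a point estimate (zero) or as a 95% interval (±0.196).

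At stake is the head-to-head conclusion, which is part of the first goal. A report of equal efficacy could not be separated from the assumption put in at the start. How often it would be reported wrongly also depends on a choice that the text leaves open.

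**Working it through.** **Inputs from the article.** Prior mean 0 and variance 0.010; equality range ±0.2; 480 participants at Phase 4 with two thirds in the experimental arms; expected pre-post effect d = 0.36. If the two experimental arms are equal in size, n = 480 × 2/3 ÷ 2 = 160 per arm.

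**Assumptions.** The variance v of latent change, in the units in which ±0.2 is expressed, is not stated. I take v = 1 and show 0.6 to 1.6. The prior is taken on the standardised scale, as the article's own 95% range implies. The posterior is approximated by combining a normal prior with a normal likelihood.

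**The article's figure.** 1.96 × √0.010 = 0.196, which rounds to the stated 0.2. Prior mass inside ±0.2 = 2Φ(0.2/0.1) − 1 = 0.954. The figure reproduces, and it shows the rule met before any data.

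**Weight of prior and data (v = 1).**
- SE² = 2v/n = 2/160 = 0.0125, so SE = 0.112.
- Data weight = 0.010/(0.010 + 0.0125) = 0.444; prior weight = 0.556.
- Posterior SD = √(1/(1/0.0125 + 1/0.010)) = 0.0745; 95% half-width 0.146.
- The prior is worth 2v/0.010 = 200 participants per arm.

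**Point-estimate reading.** Equality is declared while 0.444 × |observed| < 0.2, that is, up to an observed difference of 0.45. A true difference of 0.36 would arise if one program had the whole expected effect and the other none. Then P(equal) = Φ((0.45 − 0.36)/0.112) = 0.79. Under a flat prior it is Φ((0.20 − 0.36)/0.112) = 0.076.

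**Interval reading.** The whole 95% interval lies inside ±0.2 if |observed| < (0.2 − 0.146)/0.444 = 0.121. P(equal) is 0.722 at a true difference of 0, 0.239 at 0.2 and 0.016 at 0.36.

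**Flat prior, interval reading.** Half-width = 1.96 × 0.112 = 0.219, above 0.2. It falls below 0.2 only if v < (160/2) × (0.2/1.96)² = 0.83.

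| Result, 160 per arm | v = 0.6 | v = 1 | v = 1.6 |
|---|---|---|---|
| Prior weight | 0.429 | 0.556 | 0.667 |
| Point rule: largest observed difference called equal | 0.35 | 0.45 | 0.60 |
| Point rule: P(equal) at true 0.36 | 0.454 | 0.790 | 0.955 |
| Same, flat prior | 0.032 | 0.076 | 0.129 |
| Interval rule: P(equal) at true 0 | 0.853 | 0.722 | 0.603 |
| Interval rule: P(equal) at true 0.2 | 0.195 | 0.239 | 0.274 |
| Interval rule: P(equal) at true 0.36 | 0.003 | 0.016 | 0.044 |
| Flat-prior 95% half-width | 0.170 | 0.219 | 0.277 |

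**The case against.** The prior is disclosed in advance with its variance and rationale, and informative priors are legitimate. Open data and code are promised, so others could rerun the model under a diffuse prior. That is fair, but a later rerun does not replace a prespecified basis for the conclusion, and disclosure does not remove the overlap between prior range and margin.

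Four stronger readings are tempting, and the article does not support them.

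- **That the trial will nearly always report equality, even with one program inert.** This needs the point-estimate reading and v around 1 or more. Under the interval reading, equality at a true difference of 0.36 is declared about 2% of the time, and even for identical programs only about 72% of the time.
- **That the prior alone decides.** At v = 1 the data carry 44% of the weight (57% at v = 0.6, 33% at v = 1.6). A large enough observed difference overturns equality.
- **That the data alone could never meet the rule.** This needs the interval reading, a 95% level and v above about 0.83 at 160 per arm. With 200 per arm (no loss) and v = 1, the half-width is 1.96 × √(2/200) = 0.196, just inside. A 90% interval at 160 per arm has half-width 1.645 × 0.112 = 0.184. Success would still be uncommon.
- **That nothing supports the prior.** The Research goals section says only that the better program cannot be predicted. A symmetric prior centred on zero is consistent with that. The section on intervention content describes shared components, which is some reason to expect a small difference. It does not justify 0.2 as the margin, or judging equality from a posterior that already assumes it.

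How the latent metric is scaled may properly sit in the full plan, and no contradiction is shown. I raise it only as something for the revised wording to name.

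**Conclusion.** The concern holds. The equality range is the prior's own 95% range, so the rule is met with no data; this follows from the stated figures and needs no assumption. The posterior criterion is also unfixed, and at v = 1 that choice alone moves the chance of declaring equality at a true difference of 0.36 from about 79% to about 2%.

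The sizes rest on about 160 per arm, an assumed change variance of 1 (0.6 to 1.6) and a normal approximation. The fault in the rule does not. It concerns only the CBT-versus-mindfulness comparison, since the article states no such prior for the comparisons with the waitlist. It also does not depend on anything left to an analysis plan that is not shown: the prior, the range and the rule are all stated, and the fault lies in how they combine.

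**What to change.** Revise the Data analyses text before the arms are compared:

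1. Base the equality conclusion on the difference estimated under a diffuse prior, reported in SD units of a named latent score with its 95% credible interval.
2. Allow the word equal only if that whole interval lies inside ±0.2, and justify that margin on grounds independent of the prior.
3. Otherwise report the difference with its precision and make no equality claim.
4. Keep N(0, 0.010) as a labelled sensitivity analysis.

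The cost is revised wording and one extra model run, with no change to design or data collection. The downside is that the trial may not be able to claim equal efficacy: at 160 per arm and a change variance of 1, the diffuse-prior interval is too wide (half-width 0.22) to meet the criterion, and it is worth saying so in advance.

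### The equality rule sets a ±0.2 margin but requires no credible-interval bound or posterior probability to meet it, so under the planned prior a true difference at the margin would almost always be called equal

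*Protocol article*

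**What the plan says.** Under Research goals, the comparison of the two programmes is part of the first goal and concerns the primary outcome: "we assume that the two experimental conditions will not differ with regard to their effectiveness in reducing the primary outcome".

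Under Data analyses, the latent change models are fitted by Bayesian estimation. The difference in pre-post change between the two experimental groups gets an informative normal prior with "a mean of zero, and a small variance, that is, *N*(0, 0.010"). The article adds: "This distribution implies that 95% of the standardized differences in the means ranges from -0.2 and 0.2". The rule follows: efficacy is "considered equal if the standardized difference in the latent change scores based on the posterior distribution lies within a range of -0.2 and 0.2".

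Nowhere does the article give a credible level, an interval bound, a posterior probability or an error rate for this rule. The sample size under Participants and recruitment ("we would need *N* = 136 participants in each experimental group") is chosen "to be able to detect a pre-post difference of approximately" *d* = 0.35. That is a change within one group and does not size the comparison between programmes.

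**The concern.** A claim that two treatments are equally effective needs evidence that differences as large as the margin have been ruled out. Normally a whole interval must lie inside the margin, or the posterior probability of being inside it must be high. The rule as written asks only that the difference lie inside. An imprecise estimate near zero then counts as equality just as a precise one does.

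The informative prior makes this worse. It is centred on no difference and is about as precise as the data, so it pulls the posterior difference towards zero before the comparison with ±0.2 is made. At stake is one of the trial's main conclusions: the two programmes could be reported as equally effective when they differ by the full margin or more.

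**Working it through.** **Reproducing the plan's figure.** The prior has SD √0.010 = 0.10, and 1.96 × 0.10 = 0.196, which rounds to 0.2. The stated 95% range is correct.

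**Inputs from the article.** Margin ±0.2; prior variance 0.010; 480 participants expected in Phase 4; two thirds of participants in the experimental conditions.

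**Assumptions.** Equal split of the experimental participants: 480 × 2/3 ÷ 2 = 160 per arm. Differences are in pretest SD units with equal variances at pretest and posttest. The pre-post correlation r is not given, so 0.5 to 0.8 is shown. The estimate D is normal around the true difference δ with known standard error.

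**Formulas.**
- SE = √(2(1 − r)) × √(2/n). For r = 0.5: √1 × √(2/160) = 0.112. For r = 0.8: √0.4 × √(2/160) = 0.071.
- Literal rule, flat prior: P(|D| < 0.2).
- Literal rule, planned prior: the posterior mean is w × D with w = 0.010/(0.010 + SE²), so equality is declared when |D| < 0.2/w. For r = 0.5: w = 0.010/0.0225 = 0.444 and the cut-off is 0.45. For r = 0.8: w = 0.010/0.015 = 0.667 and the cut-off is 0.30.
- 95% interval, prior kept: posterior SD = 1/√(100 + 1/SE²), and equality needs |D| < (0.2 − 1.96 × posterior SD)/w. For r = 0.5: (0.2 − 1.96 × 0.0745)/0.444 = 0.121.
- 90% interval, flat prior: equality needs |D| < 0.2 − 1.645 × SE. For r = 0.5: 0.2 − 0.184 = 0.016.

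**Probability of declaring equality, 160 per arm.**

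| Rule | δ | r = 0.5 | r = 0.6 | r = 0.7 | r = 0.8 |
|---|---|---|---|---|---|
| Literal, planned prior | 0.20 | 98.7% | 97.7% | 95.8% | 92.1% |
| Literal, planned prior | 0.30 | 91% | 84% | 72% | 50% |
| Literal, flat prior | 0.20 | 50% | 50% | 50% | 50% |
| Literal, flat prior | 0.30 | 19% | 16% | 12% | 8% |
| 95% interval, planned prior | 0.20 | 24% | 22% | 19% | 16% |
| 90% interval, flat prior | 0.20 | 2.3% | 4.1% | 4.9% | 5.0% |
| 90% interval, flat prior | 0.30 | 0.3% | 0.4% | 0.3% | 0.1% |
| 90% interval, flat prior | 0 | 11% | 28% | 49% | 76% |

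The 50% entries hardly depend on n or r: an estimate centred on the boundary falls inside it half the time. At r = 0.5, a 95% interval with a flat prior has half-width 1.96 × 0.112 = 0.219. That exceeds the margin, so such a rule could never declare equivalence there.

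**The case against.** The strongest objection is that the rule does not say which posterior summary is meant. It speaks of the difference based on the posterior distribution, and the preceding sentence describes where 95% of a distribution lies. A credible interval could have been intended, and an analysis plan or the statistical code that the article promises might say so. This stands to the extent that the single-number reading is the literal one but not the only possible one, and the 92 to 99% and 50% figures depend on it. It does not dispose of the point. The article itself states the criterion and the verdict, and the 95% in the preceding sentence describes the prior. Even a 95% interval with the planned prior passes a true 0.20 in 16 to 24% of trials.

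Several stronger readings are tempting and are not supported:
- *Equality would be declared half the time under this plan.* The 50% belongs to a hypothetical flat prior. The plan specifies N(0, 0.010).
- *The decision rule is a defect independent of the prior.* An interval requirement limits the error to 2 to 5% only if the informative prior is removed as well.
- *The plan forbids an undecided verdict.* It says only when efficacy counts as equal. It does not say that anything else means different.
- *The margin gives away 56% of the expected benefit.* 0.20/0.36 = 0.56 holds only if both figures share a scale. The article does not define the standardizer for ±0.2, and its 0.36 comes from a meta-analysis of effects on detachment.

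**Conclusion.** The point holds in this form: the equality criterion for the primary outcome has a margin but no requirement on posterior uncertainty. Combined with the N(0, 0.010) prior, it does not control the risk of a false claim of equality. On the literal reading, with 160 per arm and r between 0.5 and 0.8 in pretest SD units, a true difference of 0.20 is called equal 92 to 99% of the time, and one of 0.30 is called equal 50 to 91% of the time. Changing only the prior leaves the rate at 0.20 at 50%. Changing only the rule to a 95% interval leaves it at 16 to 24%. Both must change to reach 2 to 5% with a 90% interval.

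The figures assume complete posttest data and a normal estimate with known standard error. Measurement error or a larger change variance would raise the standard error; with the planned prior that strengthens the pull towards zero.

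**What to change.** Replace the last sentence of the paragraph on the latent change models under Data analyses with a rule to this effect:

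*The interventions will be considered equivalent if the 90% credible interval of the standardized difference in pre-post latent change, estimated with a non-informative prior on that difference, lies wholly within -0.2 to 0.2. They will be considered different if the 95% credible interval excludes zero and equivalence is not met. Any other result will be reported as inconclusive.*

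Name the standardizer (for example the pretest SD). Report the posterior probability that the absolute difference is below 0.2. Keep the N(0, 0.010) analysis as a sensitivity analysis. Word a positive result as *differ by less than 0.2 SD*, not as *equal*.

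No new data are needed, but the change is more than wording. If the true difference is zero, equivalence is shown in 11% (r = 0.5), 28% (0.6), 49% (0.7) or 76% (0.8) of trials with 160 per arm. An 80% chance would need n = 2 × 2(1 − r) × ((1.645 + 1.282)/0.2)² per arm, which is about 429 at r = 0.5 and 172 at r = 0.8. Unless the pre-post correlation is high, an inconclusive result is likely, and the article should say so in advance.

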### Investigating processes

Complex intervention designs allow researchers to examine the underlying change mechanisms in more detail [47]. Given that unwinding is an experience that fluctuates strongly within individuals across days, we need intervention designs that capture these fluctuations and match the intervention's evaluation more closely with the behavior of interest [45]. With a pre-post-follow-up design, both the fluctuations and the trajectory of change remain unknown. By contrast, more frequent assessments paralleling the course of the intervention may reveal when the changes occur. For example, a recent mindfulness intervention study [48] found that changes in detachment followed a log-linear trajectory. This finding is in line with the dose–effect model in psychotherapy [49]. In essence, this model predicts the greatest improvements in the first phase of an intervention, followed by a phase of more stable (but improved) levels of detachment. Designs with additional assessments shed light on such trajectories of change and advance our understanding of both nonlinear improvements and phases that can be useful for stabilizing and reinforcing the change that is achieved.

With designs that include various measurements along the way, researchers can simultaneously analyze within-person processes and individual differences in these processes. For example, at the within-person level, negative activation (i.e., unpleasant mood and unpleasant discrete emotions, e.g., anger, sadness, or anxiety) and high tense arousal may represent the key variables that impair recovery [50] and serve to maintain PT. Negative activation (NA) may impede recovery because individuals experience and relive job stressors even after long periods of not working and might not even recover fully during sleep due to its job-related fragmentation [51]. Also, NA and both recovery and PT may be reciprocally related (i.e., not only does NA impede recovery/maintain PT, but low recovery/high levels of PT may, in turn, maintain NA). Shipp and Cole [52] argued that "considering the role of feedback loops, cycles, and spirals is a natural next step for within-person explanatory research" (p. 12). The reciprocal relations between recovery and PT on the one side and NA on the other side may create a loss cycle [53]. This sustained mental and affective arousal may, in turn, be associated with symptoms of strain, such as impaired sleep [54].

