#### Process assessment

The measurement burst design will include various phases of intensive longitudinal assessments. In Phases 2, 4, and 5, participants will receive links to self-reports four times per day from Monday morning through Saturday morning. We will prompt participants in the morning, directly after work, at 8 pm, and before bedtime. The assessments will include items on work-related variables (e.g., job demands and resources, work engagement), mental health variables (e.g., fatigue, sleep quality, stress, recovery), and personal characteristics (e.g., affect regulation, negative activation, personal resources, and working hours). All items refer to the state aspects of the constructs. Table 1 presents the measures, and the project's Codebook on the OSF repository offers more details.

During the 6 weeks of the intervention, we will implement 1 day of experience sampling each week with a total of five assessments (beginning on Tuesday at bedtime followed by four assessments on Wednesday). The measurements will parallel those in Phases 2, 4, and 5.

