We will use the assessments paralleling the interventions to estimate a Growth Model separately in each group. To account for potential nonlinear growth over time, we will implement free time scores when estimating the slope growth factor in each group. The time score in the first week will be fixed to zero (centering point), whereas the time score in the sixth week will be fixed to one. Hence, the mean of the slope growth factor will represent the average rate of change from Week 1 to Week 6.

The Dynamic Structural Equation Modeling (DSEM) [90] approach will be applied to the measurement burst part of the study. DSEM is suitable for addressing the particular issues of (a) intensive longitudinal data, (b) autoregressive and cross-lagged within-person effects, and (c) different time-lags (between and within persons). DSEM combines four modeling techniques: multilevel modeling, time-series modeling, structural equation modeling, and time-varying effects modeling. The multilevel part of DSEM will allow us to model the correlations that are due to individual-specific effects. The time-series part of DSEM will enable us to model the correlations that are due to the proximity of observations. The structural equation modeling part will be based on correlations between different variables. The time-varying effects modeling will be based on correlations that are due to the same stage of development. This flexibility makes DSEM suitable for testing the hypotheses in our study. The postulated mediation and moderation effects will apply to the within-day level (Level 1) of analysis. To test the time course of the processes, job stressors will be measured directly after work. Negative activation, detachment, and work-related PT will be measured in the evenings. Strain variables and the state of being recovered will be assessed in the mornings. This procedure will allow us to test for autoregressive and cross-lagged associations between the constructs. Recovery strategies, mindfulness, and emotion regulation are also Level 1 variables and can be accounted for in the DSEM. Hypotheses focusing on the interventions’ effectiveness at a daily level can be implemented as a cross-level predictor. Moreover, given that the study will manipulate work-related PT, changes in the intercepts, variances, and covariances of the variables are expected and will be modeled as random effects.

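### The weekly growth model starts its clock after training has opened and leaves out the parallel pre-training measures, so change before the Week 1 assessment goes into the intercept

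*Protocol article*

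**What the plan says.** Data analyses in the protocol article sets the data for the model: "We will use the assessments paralleling the interventions to estimate a Growth Model separately in each group". On shape it says that "we will implement free time scores when estimating the slope growth factor in each group". Two time scores are fixed: "The time score in the first week will be fixed to zero (centering point", and "whereas the time score in the sixth week will be fixed to one". The stated meaning of the result is that "the mean of the slope growth factor will represent the average rate of change from Week 1 to Week 6".

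Three other places bear on this:

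- Study design: the experimental groups get access to training immediately after Phase 2, the first week of intensive assessment. The waitlist groups answer the same questionnaires in every phase.
- Process assessment: Phase 2 runs from Monday morning to Saturday morning with four prompts a day. Each weekly assessment during training runs from Tuesday bedtime through Wednesday. Of the weekly content it says: "The measurements will parallel those in Phases 2, 4, and 5".
- Investigating processes: assessments during the intervention are justified as a way to see when change happens. The section cites a log-linear course for detachment in a previous mindfulness study and a dose-effect model, of which it says that "this model predicts the greatest improvements in the first phase of an intervention".

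**The concern.** A growth curve describes change from its zero point onward. Here the zero point is an on-treatment measurement. Whatever a programme achieves between access and the first Tuesday/Wednesday becomes part of the Week 1 level and not part of the change.

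What is at stake is the description of the trajectory, which is the reason given for collecting weekly data. If gains come early, as the cited literature suggests, the curve begins after its first step, and the slope understates the change from before training to Week 6. The faster a programme works, the more of its effect moves from slope to intercept. A pre-training point on the same measures is already scheduled and goes unused in this model.

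**Working it through.** The plan gives no figure for this, so there is none to reproduce. The check is how much of the change from access to the Week 6 assessment has already happened at Week 1.

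**Inputs**

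- Spacing: Week 1 to Week 6 is 5 weeks, or 35 days (weekly Tuesday/Wednesday assessments, Process assessment).
- Days from access to the Week 1 assessment, d: the access day is not stated. Phase 2 ends on Saturday morning. Access on that Saturday puts Wednesday at day 4; access on Monday puts it at day 2. I take d = 2 to 5 as an assumption.
- Shape of change, f: not fixed by the article, which allows for non-linear growth and cites a log-linear course without giving its time unit. I use three curves.

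**Formula:** omitted share = f(d) / f(d + 35)

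| d (days) | Linear, f = d | Log in weeks, f = ln(1 + d/7) | Log in days, f = ln(1 + d) |
|---|---|---|---|
| 2 | 2/37 = 5% | 0.251/1.838 = 14% | 1.099/3.638 = 30% |
| 3 | 3/38 = 8% | 19% | 38% |
| 4 | 4/39 = 10% | 0.452/1.883 = 24% | 1.609/3.689 = 44% |
| 5 | 5/40 = 13% | 0.539/1.904 = 28% | 1.792/3.714 = 48% |

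**Is the omitted step the largest one?** With d = 4, the steps as shares of the total are:

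| Step | Log in weeks | Log in days |
|---|---|---|
| Access to Week 1 (omitted) | 24% | 44% |
| Week 1-2 | 26% | 24% |
| Week 2-3 | 17% | 13% |
| Week 3-4 | 13% | 9% |
| Week 4-5 | 11% | 7% |
| Week 5-6 | 9% | 5% |

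The answer depends on the curve and the access day. For log in weeks, with t = d/7, the omitted step exceeds the Week 1-2 step only if ln(1 + t) > ln[(2 + t)/(1 + t)]. That is t² + t − 1 > 0, so t > 0.618 weeks, about 4.3 days. For log in days the condition is (1 + d)² > 8 + d, which holds from d = 3.

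**Do other analyses supply the missing piece?** The latent change models use pretest, posttest and follow-up only, and Investigating processes itself says that such a design leaves the course of change unknown. The dynamic structural equation models are assigned to the bursts. Neither specifies a trajectory from before training through Week 6.

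**The case against.** The strongest reply is that the article labels its slope correctly as change from Week 1 to Week 6 and does not present it as the total effect. Change from before training is estimated elsewhere, and the free time scores pick up everything after Week 1. Only the first few days are lost. All of this stands. It limits the point to the trajectory analysis but does not supply the missing first step.

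A second reply concerns the remedy. Phase 2 is the participants' first week of dense prompting, so initial reactivity could enter the slope. That is fair. The waitlist groups go through the same Phase 2, however, so a contrast with them removes reactivity that is common to the arms.

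A reader might infer several stronger things, which the document does not support:

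- *That the model drops the change the plan expects to be largest.* The background reports one previous study of detachment and a general dose-effect model, and does not define the first phase. Under log in weeks with access on Saturday, the Week 1-2 step is slightly larger than the omitted one, and the model captures it.
- *That the waitlist time scores are unidentified because no mean change is expected there.* They are also identified through the covariances when the slope variance is not zero. A rank check of the six-occasion model with slope mean zero gave full rank (15 of 15) at slope variances 0.2 and 0.05. Rank fell to 11 only when mean and variance were both zero. The article also does not say that it expects no mean change in the waitlist.
- *That fitting separately rules out group contrasts.* The words "to estimate a Growth Model separately in each group" do not exclude a multigroup model. The latent change models are described in similar terms and are then named as multigroup models.
- *That a planned comparison of slopes between programmes is biased.* No such comparison is specified for the growth model. The specified comparison of programmes uses pre-post change scores.

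**Conclusion.** The point holds in a limited form. Time zero is an on-treatment assessment, the parallel Phase 2 measures are left out of the model, and change before Week 1 is absorbed by the intercept. That is a poor fit with the purpose given for the weekly data.

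The omitted share is about 5-13% if change is linear, 14-28% if logarithmic in weeks and 30-48% if logarithmic in days, for a first assessment 2 to 5 days after access. Both the curve and the access day are my assumptions. I do not convert these shares into standard deviations. The d = 0.36 in the article is a meta-analytic effect on detachment and need not apply to the weekly state measures.

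The primary pre-post analysis is unaffected, so this is an inexpensive improvement to a process analysis and not a threat to the efficacy conclusion.

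**What to change.** Add the Phase 2 Tuesday-bedtime and Wednesday occasions, which match the weekly schedule, as time score 0. Free Weeks 1 to 5 and fix Week 6 at 1. The slope mean then represents change from before training to Week 6. Contrast that change in each training arm with the waitlist, so that initial reactivity to the dense Phase 2 prompting cancels.

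If the present coding is kept, state that the slope excludes change before the Week 1 assessment, and compare Week 1 levels between each training arm and the waitlist. Under randomisation that comparison shows the early change.

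Either option changes analysis wording only. The occasions are already scheduled, so participants carry no extra burden. The first option adds one free time score per group and relies on reactivity being alike in the training and waitlist arms.
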